#### Data analysis

The LCTU Trial Statistician will be responsible for planning, monitoring and carrying out analyses, supervised by a senior statistician. Statistical analysis will be undertaken according to a prespecified statistical analysis plan (SAP) written prior to database lock and reported following Consolidated Standards of Reporting Trials statements. The baseline characteristics of the participants will be summarised by group. Continuous variables will be summarised using mean and SD, or median and IQR if data do not have a symmetric distribution. Categorical variables will be summarised with counts and percentages. The primary analysis of the primary outcome will be carried out in the ITT population using a mixed effects model with participant as a random effect to account for repeated measures over time. Each participant will contribute up to three repeated outcome measures to the model in addition to the baseline SCr. The model will be adjusted for the stratification and minimisation variables (age, sex, baseline CKD stage and presence of tissue loss). Secondary outcomes will be analysed on a complete case population and reported similarly to the primary outcome using appropriate methodology to compare randomised groups; binary outcomes using logistic regression, continuous outcomes using linear regression or, where not normally distributed, using appropriate non-parametric methods.

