## Methods and analysis

### Trial design

Multicentre, prospective, open-label, parallel-group RCT. The trial will also include a health economic evaluation to assess cost-effectiveness from both an NHS and a wider English societal perspective.

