### Outcomes

Outcomes and assessments are based on national and international consultation with AKI experts, our national stakeholder/patient survey, patients’ opinions during our patient involvement work and our previous/ongoing randomised and observational research relating to renal decline in vascular patients.^1^

We plan to evaluate the impact on kidney function postendovascular revascularisation in the RCT arms both in the short term (AKI) and at 90 days (medium term). We will include creatinine measurements at 2, 30 and 90 days, powered to detect a clinically meaningful difference in serum creatinine (SCr) at 90 days. These three SCr measurements will also allow us to compare AKI incidence based on the Kidney Disease Improving Global Outcomes (KDIGO) definition of AKI between groups and calculate/compare the incidence of major adverse kidney events at 90 days (MAKE outcome). This will provide novel information on the clinical value of using the proposed intervention, addressing the relevant evidence gap and leading to adoption of the intervention in the NHS, for the immediate benefit of patients in this high-risk group. We have chosen not to use AKI incidence at 2 days as the primary outcome, as it does not allow us to evaluate medium-term renal injury and would also necessitate recruitment of a prohibitively large sample of patients, without adding clinical information that would aid translation to clinical care.

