### Primary outcome

Log SCr measured from the blood sample taken at 2, 30 and 90 days (part of the standard of care) after endovascular revascularisation.

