#### Trial management

The KID trial will be managed by the LCTU, a UK Clinical Research Collaboration-registered CTU (registration number 43), colocated with the chief investigator (CI) at the University of Leicester (UoL). The LCTU will provide trial management, statistical data and quality oversight support throughout the trial duration. The study is sponsored by the UoL.

Trial oversight will be provided through three key governance structures: the Trial Management Group (TMG), the Trial Steering Committee (TSC) and the DMC. The TMG will meet weekly or as needed and will be responsible for the day-to-day operational management of the trial. It will include the CI, coapplicants, the trial manager, the lead statistician and two lay coapplicants. The lay coapplicants will also liaise with an independent lay advisory group to ensure patient-centred conduct and delivery of the trial. The TSC will meet at least every 6 months. It will be chaired by an independent member and include external clinical, statistical and lay representatives. The TSC will provide high-level oversight, ensure adherence to the protocol and advise on trial progress and conduct.

The DMC will meet separately, prior to each TSC meeting. Comprising independent clinical and statistical experts, including an independent Chair, the DMC will review accumulating trial data with respect to participant safety and data integrity. It will make recommendations to the TSC regarding the continuation, modification or termination of the trial based on these reviews.

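### The primary treatment contrast is not named: the sample size supports the average over three visits, one section claims power at day 90, and the SAP deadline does not guarantee a choice blind to results

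*Protocol article*

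**What the plan says.** **The outcome and its contrast.** The Primary outcome section of the protocol article reads "Log SCr measured from the blood sample taken at 2, 30 and 90 days" and names neither a summary over visits nor a leading visit. The Outcomes section says the trial is "powered to detect a clinically meaningful difference in serum creatinine (SCr) at 90 days". The Sample size calculation section instead powers a mean difference of 0.075 log units at all three visits. Data analysis, and Planned analyses for primary and secondary outcomes, both specify an intention-to-treat mixed model with a random participant term and baseline adjustment. Neither says whether the reported effect is common to the three visits, specific to day 90, or one effect per visit.

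**When the analysis is fixed, and by whom.** The design is "Multicentre, prospective, open-label, parallel-group RCT". The Data analysis section has the analysis done "according to a prespecified statistical analysis plan (SAP) written prior to database lock" and gives no earlier milestone. On roles it says: "The LCTU Trial Statistician will be responsible for planning, monitoring and carrying out analyses, supervised by a senior statistician". Under Trial management, the lead statistician belongs to the group that runs the trial day to day, while "the DMC will review accumulating trial data with respect to participant safety and data integrity". The article does not say who prepares the data monitoring committee's reports, or whether the SAP authors are kept from outcome data by arm.

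**The concern.** The average over visits and the day-90 effect are different questions. The average gives two-thirds of its weight to days 2 and 30, so it mixes the early response to contrast with the later state. The day-90 effect is what the Outcomes section presents as the medium-term result. The two also differ in precision, so a power statement true of one is not true of the other.

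Timing matters because the choice is open. A deadline of database lock protects prespecification well when allocation stays hidden until lock. In an open-label trial it does not by itself show that the SAP came before knowledge of creatinine by arm. If the contrast were chosen with that knowledge, the 5% error rate of the main claim would no longer hold. Even without any such choice, a reader of the Outcomes section would credit the day-90 comparison with 90% power.

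**Working it through.** **Inputs** (Sample size calculation section): SD 0.25 log units; difference 0.075; correlation ρ = 0.67 among baseline and the three follow-up measures; alpha 0.05; power 90%; 156 patients (78 per group); 10% drop-out; 174 recruited (87 per group). Assumed here: two-sided alpha (sidedness is not stated, but two-sided reproduces the figure), equal correlation between all time points, and the normal approximation.

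**Formula.** n per group = 2 × (1.960 + 1.282)² × SD² × v / 0.075². With baseline adjustment and r follow-up visits averaged, v = [1 + (r − 1)ρ]/r − ρ².

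**1. Reproduce the stated sample size (average, r = 3).**
- v = (1 + 2 × 0.67)/3 − 0.67² = 0.7800 − 0.4489 = 0.3311
- n = 2 × 10.507 × 0.0625 × 0.3311 / 0.005625 = 77.3, so 78 per group, 156 in total
- 156/0.9 = 173.3, so 174

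Both figures match the plan. Power at 78 per group is 90.3%.

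**2. Day 90 alone, adjusted for baseline (r = 1).**
- v = 1 − 0.4489 = 0.5511, so the adjusted SD is 0.25 × √0.5511 = 0.1856
- n = 128.7, so 129 per group: 258 in total, 287 with 10% drop-out
- At 78 per group: 0.075 / (0.1856 × √(2/78)) = 2.524; power = Φ(2.524 − 1.960) = 71%
- At 87 per group: 2.665; power = 76%

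**3. Other readings.**

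| Analysis (0.075, 90% power) | n per group |
|---|---|
| Average of three visits, baseline-adjusted, two-sided | 78 |
| Same, one-sided | 64 |
| Average of change from baseline | 103 |
| Average without baseline | 183 |
| Day 90 alone, baseline-adjusted | 129 |

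Of the readings tried, only the first gives 78.

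**4. Type I error if the contrast were picked on results.** After baseline adjustment, the correlation between two visits is (0.67 − 0.4489)/(1 − 0.4489) = 0.401. The correlation between the averaged test and the day-90 test is √(0.3311/0.5511) = 0.775. Simulation under no treatment effect, each test at two-sided 0.05:

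| Basis for choosing between average and day 90 | Type I error |
|---|---|
| Contrast fixed in advance | 5.0% |
| Larger test statistic at 25% of the information | 6.1% |
| Larger test statistic at 50% of the information | 7.0% |
| Better of the two final results | 7.9% |

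**The case against.** Committing to an SAP before lock is ordinary protocol language and sets a latest date, not the intended one. A journal article may leave the SAP's version date, statistician blinding and the source of committee reports to documents not shown, so their absence is no fault. A reader might infer from the open-label design and from "The LCTU Trial Statistician will be responsible for planning, monitoring and carrying out analyses" that the SAP will be written with creatinine by arm in view. The article does not support that. Open-label means that individual allocations are known; it does not mean that the statistician sees outcomes tabulated by arm. Accumulating data go to an independent committee for safety and data integrity, a senior statistician supervises, and no interim efficacy analysis is described. This part of the objection stands.

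It is also fair to say that the primary analysis is far from undefined. Population, model class and baseline adjustment are fixed, and the sample size points to the average. A reader might go further and count days 2 and 30 as candidate primaries, which would bring the worst-case error to about 14%. No section offers either visit alone as primary, so that figure does not apply.

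What the objection does not remove is the conflict inside the article. The Outcomes section claims power at day 90, the sample size arithmetic does not deliver it, and no section says which contrast decides the trial.

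**Conclusion.** The point holds in a limited form.

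- **Established:** no single primary contrast is named, and the Outcomes section conflicts with the sample size calculation. The design has 90% power for the baseline-adjusted average, but 71% (78 per group) to 76% (87 per group, no losses) for a difference of 0.075 at day 90 alone.
- **Permitted but not established:** the contrast could be settled after creatinine by arm is known, because lock is the only stated SAP deadline. The article is silent in both directions on whether an SAP author will see such data.
- **Size of that risk:** a type I error of at most about 8% rather than 5%, and about 6–7% if the choice rested on a quarter to a half of the data. These figures assume a deliberate, results-driven choice, which nothing in the article suggests.

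The power figures rest on the plan's SD and its common correlation of 0.67. A day-90 correlation with baseline different from 0.67 would move the 71% and 76%.

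**What to change.** 1. In Primary outcome, and in Planned analyses for primary and secondary outcomes, state that the primary contrast is the treatment effect on log creatinine averaged over days 2, 30 and 90, adjusted for baseline, with the day-90 effect secondary. This is the contrast the sample size supports.
2. In Outcomes, replace the claim of power at 90 days with power for the visit-averaged effect. If day 90 is mentioned, give its power as about 71–76% for the same difference.
3. In Data analysis, replace the lock deadline with an SAP signed and dated before any of its authors sees creatinine by arm. Later amendments remain possible if dated and justified. If the full protocol or SAP already says this, one confirming sentence is enough.

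The cost is earlier statistician time, a few lines of wording and a less favourable stated power for day 90. The sample size and visits do not change. If the day-90 effect is the one wanted as primary, 90% power for 0.075 would need 129 per group (287 with drop-out).

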### Statistical considerations

#### Sample size calculation

174 patients (87 per group) provide 90% power to detect clinically meaningful differences. Based on our preliminary data (observational AKI study of 2021 patients with PAD/CKD treated in three sites and a pilot study on the use of CO_2_ in PAD procedures),^78 15^,^17^ we expect the SD of log SCr values at 2, 30 and 90 days to be 0.25 log (µmol/L). We assume the correlation of the baseline, 2, 30 and 90-day measures to be 0.67, which is conservative. With these assumptions, a sample size of 156 patients (78 per group) would have a 90% power to detect a mean difference of 0.075 log (µmol/L) in SCr values (effect size of 0.3) at 2, 30 and 90 days postsurgery, between intervention and control groups with an alpha value of 0.05. Allowing for a 10% drop-out, 174 will be recruited. This sample size will also allow us to assess for a 20% reduction in the volume of iodinated contrast used in those having the intervention versus control (median of 70 mL of iodinated contrast used in our published series without CO_2_). In order to ensure the population remained truly per intention-to-treat (ITT) for the primary outcome, multiple imputation will be implemented to deal with missing data in instances where participants are missing any of the SCr values. Values will be predicted using a multivariate normal regression equation with 20 imputations being used.

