#### Assignment of interventions and randomisation

1:1 electronic randomisation. Minimisation based on CKD stage, age, diabetes and tissue loss.

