### Statistical methods

#### Planned analyses for primary and secondary outcomes

The primary analysis will be performed on an ITT basis, including all randomised participants as allocated. The primary outcome—log SCr at 2, 30 and 90 days postprocedure—will be analysed using a mixed-effects model with participant as a random effect to account for repeated measures over time. The model will adjust for baseline log SCr, stratification and minimisation factors (age, sex, baseline CKD stage and presence of tissue loss).

Secondary outcomes will be analysed using appropriate statistical methods: binary outcomes (eg, AKI incidence, MAKE) will be compared between groups using logistic regression; continuous outcomes (eg, contrast volume, QoL scores) will be analysed using linear regression, or non-parametric tests if data are not normally distributed. Time-to-event data, if applicable, will be analysed using survival analysis methods such as Kaplan-Meier estimates and Cox proportional hazards regression. All analyses will be conducted using validated statistical software according to a prespecified SAP.

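### The primary model's list of allocation factors does not match the stated minimisation: diabetes is missing, sex is added, and no stratification factor is named

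*Protocol article*

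**What the plan says.** Three sections of the protocol article bear on this.

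- **Assignment of interventions and randomisation:** "1:1 electronic randomisation", followed by "Minimisation based on CKD stage, age, diabetes and tissue loss". No stratification factor is mentioned, and sex is not listed.
- **Data analysis:** "The model will be adjusted for the stratification and minimisation variables (age, sex, baseline CKD stage and presence of tissue loss". Diabetes is not listed.
- **Planned analyses for primary and secondary outcomes:** "The model will adjust for baseline log SCr, stratification and minimisation factors (age, sex, baseline CKD stage and presence of tissue loss". This is the same list, with baseline log serum creatinine named alongside it. Diabetes is again absent.

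**The concern.** Both analysis sections state a principle (adjust for the factors used in allocation) and then a list meant to carry it out. Set against the randomisation section, the list does not carry out the principle. A statistician following the principle would fit diabetes and would not need sex. One following the list would fit sex and leave diabetes out. These are different primary models.

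Two things are at stake. First, one published statement about the trial is wrong: either the allocation is misreported or the model departs from its own description. Second, if diabetes is minimised on but left out of the model, the arms are balanced on it by design while the model-based standard error is computed as if they were not. To the extent that diabetes is prognostic once baseline creatinine and the other covariates are fitted, the standard error is too large, the test is conservative and a little power is lost.

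**Working it through.** **Step 1. Compare the lists.**

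| Factor | Randomisation section | Both analysis sections |
|---|---|---|
| CKD stage | yes | yes |
| Age | yes | yes |
| Tissue loss | yes | yes |
| Diabetes | yes | no |
| Sex | no | yes |
| A named stratification factor | none | none (the word is used, but no factor is identified as one) |

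Three factors are shared, and one is unique to each side. No other section reconciles them.

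**Step 2. Reproduce the plan's sample size.** Inputs from Sample size calculation: target "90% power to detect a mean difference of 0.075 log (µmol/L) in SCr values (effect size of 0.3"; SD 0.25 on the log scale at each follow-up; a common correlation of 0.67 between the baseline and follow-up values; alpha 0.05, taken as two-sided; 78 per group; 10% drop-out.

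- Variance factor for the mean of three follow-up measures, adjusted for baseline: (1 + 2 × 0.67)/3 − 0.67² = 0.7800 − 0.4489 = 0.3311.
- Effective SD: 0.25 × √0.3311 = 0.1439.
- n per group: 2 × (0.1439 × (1.960 + 1.282)/0.075)² = 77.3, so 78 per group and 156 in all. 156/0.9 = 173.3, so 174.
- At 78 per group: SE = 0.1439 × √(2/78) = 0.02303; 0.075/0.02303 = 3.256; power = Φ(3.256 − 1.960) = 90.3%.

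The stated figures reproduce. The calculation uses no minimisation covariate, so the mismatch does not alter the sample size.

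**Step 3. Size of the effect if diabetes is minimised on but not fitted.** The article gives no measure of how strongly diabetes predicts log serum creatinine. Let R² be the share of the residual variance it explains after the fitted covariates. The values 2%, 5% and 10% are assumptions. Assume also near-perfect balance on diabetes. The true SE is then √(1 − R²) times the SE that the model without diabetes reports.

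- Excess interval width: 1/√(1 − R²) − 1.
- True type I error: 2Φ(−1.96/√(1 − R²)).
- Power without diabetes in the model: Φ((3.256 − 1.96)/√(1 − R²)). The critical value is set by the inflated SE, but the estimate varies with the smaller true SE.
- Power with diabetes in the model: Φ(3.256/√(1 − R²) − 1.96).

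| Assumed R² | Interval too wide by | True type I error | Power, not fitted | Power, fitted | Gain (points) |
|---|---|---|---|---|---|
| 2% | 1.0% | 4.8% | 90.5% | 90.8% | 0.3 |
| 5% | 2.6% | 4.4% | 90.8% | 91.6% | 0.8 |
| 10% | 5.4% | 3.9% | 91.4% | 92.9% | 1.5 |

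The unfitted power must include the benefit of balance. Setting the fitted figures against a flat 90.3% would give gains of about 0.5, 1.3 and 2.6 points. That overstates the loss, because it applies the balance to type I error but not to power.

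**The case against.** The best defence has four parts.

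- **The randomisation section may be the one in error.** It is two short sentences in a condensed article, whereas the model list appears twice in the same form. This stands. The article cannot show which list is right, so a reader should not infer that diabetes has certainly been dropped from a correct allocation list. The contradiction remains whichever list is right.
- **Sex might be the stratification factor that the analysis sections allude to.** The randomisation section describes no stratification, and this reading would not explain why diabetes is absent. Adjusting for sex as a prespecified prognostic covariate is acceptable in itself; only its label as an allocation factor is in doubt.
- **The analysis plan may settle the matter.** The article commits to one before database lock, and both analysis sections name the same covariates. A reader might infer that the covariate set is open to choice after the data are seen. The documents do not support that. The fault is that two explicit statements conflict, which is different from a detail deferred to the analysis plan.
- **The consequence is small and runs in the safe direction.** This also stands. No bias or inflated false-positive rate follows, and with baseline creatinine and CKD stage in the model only the remaining contribution of diabetes matters.

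A reader might also want to add centre to the model or extend the same covariates to the secondary outcomes. Neither list claims centre as an allocation factor, so its absence contradicts nothing, and both choices are commonly left to the analysis plan. They are not part of this point.

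**Conclusion.** The primary model as written contradicts the stated allocation, and the text alone shows it. This should be fixed because it concerns the covariate set of the confirmatory analysis, not because the numerical cost is large.

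The size is conditional on three things: that the randomisation section is correct, that balance on diabetes is close to perfect, and that partial R² lies in the assumed 2% to 10% range. Weaker balance or a weaker predictor makes the effect smaller. If instead the model list matches the actual allocation, there is no loss of efficiency, and the error is in the description of the randomisation.

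A stronger reading, that the trial is materially underpowered or its primary test invalid, is not supported. Under these assumptions power without diabetes in the model stays above 90%, and the type I error is below 5%.

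**What to change.** 1. Check which factors the live randomisation system uses.
2. Make the three sections agree with it: Assignment of interventions and randomisation, Data analysis, and Planned analyses for primary and secondary outcomes.
3. Adjust the primary model for baseline log serum creatinine plus every factor actually used in allocation. If the randomisation section is correct, that means adding diabetes.
4. Keep sex only as a separately named, prespecified prognostic covariate, unless it proves to be an allocation factor.
5. Delete the word stratification, or name the factor it refers to.

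Settle this before any comparative data are examined. The cost is a line or so of text in each section and the matching line in the analysis plan. If diabetes drives allocation, it is already recorded at randomisation, so no new data are needed. The sample size does not change.
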